## Abstract

**Background:**

Routine use of surgical drains after abdominal operations has largely been abandoned over the past decades. Studies have failed to demonstrate benefits of routine drainage following liver, gallbladder, gastric, and colorectal surgeries.

Until recently, intraoperative placement of abdominal drains was the gold standard in pancreatoduodenectomies (PDs) due to concerns about uncontrolled postoperative pancreatic fistula (POPF). A large randomized trial in 2014 reported increased mortality in patients without postoperative drain placement. However, as the study did not stratify participants based on their preoperative risk of developing a POPF, further research is needed.

Limited evidence from a non-randomized cohort suggests that omitting drains may be safe in very low-risk settings. However, a larger comparative study, including a broader range of PD cases, is necessary to confirm these findings.

**Methods:**

This is a two-arm, randomized, controlled, non-blinded, multicenter trial comparing intra-abdominal drain placement with no drain placement during planned pancreatoduodenectomies (PDs).

Eligible patients who meet the inclusion criteria will be assessed for their individual risk of postoperative pancreatic fistula (POPF) using a risk scoring system. They will then be randomized into either the drain placement or no drain placement group.

The groups will be compared using the chi-square test for categorical variables and Fisher’s exact test. Logistic regression models will be used to calculate odds ratios for morbidity. Univariable and multivariable models will assess the impact of drain placement on clinical outcomes.

**Discussion:**

This trial aims to determine whether omitting routine intraoperative drain placement reduces the risk of complications in patients undergoing pancreatoduodenectomy (PD). It will provide level 1 evidence on the association between routine intra-abdominal drainage and postoperative complications in patients with a low to intermediate risk of developing a postoperative pancreatic fistula (POPF). The findings will contribute to future treatment guidelines by expanding the available knowledge on optimal drainage strategies.

**Trial registration:**

ClinicalTrials.gov Identifier: NCT05270564. Registered on February 16 2022.

**Supplementary Information:**

The online version contains supplementary material available at 10.1186/s13063-026-09762-9.

## Administrative information

Note: the numbers in curly brackets in this protocol refer to SPIRIT checklist item numbers. The order of the items has been modified to group similar items (see http://www.equator-network.org/reporting-guidelines/spirit-2013-statement-defining-standard-protocol-items-for-clinical-trials/).

## Introduction

### Background and rationale {6a}

The routine placement of surgical drains following abdominal operations has largely been abandoned over the past decades. Previous studies have failed to demonstrate benefits of routine drainage following liver [1], gallbladder [2], gastric [3], and colorectal surgery [4, 5]. However, intraoperative placement of an abdominal drain remains the gold standard in pancreatoduodenectomies (PDs) due to concerns about uncontrolled postoperative pancreatic fistula (POPF). Uncontrolled POPF can have severe consequences, including intra-abdominal abscesses and post-pancreatectomy hemorrhage (PPH), which may lead to mortality. The rationale for drain placement is to control and remove collected fluid, potentially mitigating the impact of a fistula if one develops. However, the routine use of drains has been increasingly questioned.

Large retrospective cohort studies [6–10], a single-institution randomized controlled trial (RCT) [11], and multiple meta-analyses [12–15] have failed to show a clear benefit of routine drainage. Some reports suggest that patients without routine drainage experience lower rates of wound infection and delayed gastric emptying [8], as well as reduced hospital readmission rates [9]. Additionally, routine drainage has been associated with prolonged hospital stays [6, 9].

More recently, a non-randomized sub-cohort of PD patients with a very low risk of POPF, as determined by the fistula risk score [16], has been managed without drains or with early drain removal, without subsequent fistula development [17]. Furthermore, multiple studies have shown significantly lower rates of POPF and shorter median hospital stays in patients randomized to drain removal on postoperative day (POD) 3 compared to POD 5 [18, 19]. Additionally, delayed drain removal appears to increase postoperative morbidity, as higher rates of intra-abdominal infections have been observed in patients whose drains were removed on POD 8 compared to POD 4 [20].

To date, available evidence has primarily focused on the safety of a no-drain policy or early drain removal. In line with recent data demonstrating the superiority of a no-drain approach in left-sided pancreatic resections, this question needs further exploration in the context of PD [21]. The risk of POPF after PD is well known to correlate with pancreatic remnant characteristics, with soft, fatty glands and small duct diameters carrying the highest risk [22, 23]. Additionally, patient factors such as body mass index (BMI) and comorbidities have been linked to a higher risk of fistula formation [24, 25], as reflected in various POPF predictive scores [26, 27]. A preoperative risk score, incorporating pancreatic duct diameter and BMI, was developed by Roberts et al. [25] to aid in patient selection.

Calls for a large, randomized trial have been made, and in 2014, a multicenter study reported higher mortality among patients who did not receive drains [28]. However, this study did not account for variations in POPF risk based on preoperative or intraoperative predictors. Patients were included regardless of whether they had a high, intermediate, or low risk of developing POPF. Notably, among the 10 fatalities in the study, 8 had a soft pancreas, and 6 had a pancreatic duct diameter smaller than 3 mm. In their conclusion, the authors emphasized the need for studies incorporating predictive factors to identify patients who may safely undergo PD without routine drainage.

For this reason, the current RCT aims to evaluate the role of surgical drains in patients with a low or intermediate risk of developing pancreatic fistulae.

### Objectives {7}

The study hypothesis is that omitting intraoperatively placed drains decreases the morbidity rate after PD in patients with low to intermediate risk of POPF.

### Trial design {8}

DRAIN1 is a two-armed, randomized, controlled, non-blinded, multicenter trial.

## Methods: participants, interventions, and outcomes

### Study setting {9}

The DRAIN1 trial is conducted in (academic) university hospitals in Sweden. A list of study sites can be obtained from ClinicalTrials.gov (NCT05270564).

### Eligibility criteria {10}

#### Inclusion criteria

Patients must meet the following criteria to be included in the study:Undergoing pancreatoduodenectomy (PD), regardless of sex. Predicted pancreatic fistula risk score of ≤ 10, based on the predictive score of Roberts et al. that considers only body mass index and pancreatic duct width [25].Age ≥ 18 years.Provision of written informed consent.Expected survival time of more than 6 months.

#### Exclusion criteria

Patients meeting any of the following criteria will be excluded:Predicted high risk of postoperative pancreatic fistula (i.e., risk score > 10, according to Roberts et al. [25]).Presence of intra-abdominal abscess or infection.American Society of Anesthesiologists (ASA) score > 3.Pregnancy.Expected lack of compliance.

#### Eligibility criteria for participating centers

Centers must have a dedicated pancreatic surgery unit performing at least 40 PDs per year to be eligible for participation.

### Who will take informed consent? {26a}

Written informed consent is obtained by surgeons participating in pancreatic surgery and perioperative treatment of the actual patients.

### Additional consent provisions for collection and use of participant data and biological specimens {26b}

The consent form does not ask participants whether they agree to the use of their data if they choose to withdraw from the trial. Consequently, data from patients who withdraw will not be included in the analysis. Additionally, participants are not asked for permission to allow the research team to share relevant data with other researchers or regulatory authorities. This trial does not involve the collection or storage of biological specimens.

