## Assignment of interventions: blinding

### Who will be blinded {17a}

The DRAIN1 trial is an open-label trial.

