### Plans to promote participant retention and complete follow-up {18b}

Due to the short follow-up period (90 days), complete follow-up is anticipated without the need for specific retention measures. Since the intervention occurs as a single event during surgery, the dropout rate is expected to be low. Additionally, as the informed consent does not request permission to use previously collected data or gather additional data upon withdrawal, no specific plan exists for handling such data.

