## Statistical methods

### Statistical methods for primary and secondary outcomes {20a}

The statistical analysis will follow the intention-to-treat principle. Baseline characteristics will be presented as means with standard deviations or medians with interquartile ranges, depending on data distribution. The chi-square test will be used for categorical variables when the expected count is ≥ 5; otherwise, Fisher’s exact test will be applied. Logistic regression models will be used to estimate odds ratios for morbidity risk and drain use. Univariable and multivariable models will be employed to assess the impact of drain placement on outcomes.

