### Methods in analysis to handle protocol non-adherence and any statistical methods to handle missing data {20c}

Patients allocated to no-drain treatment but receiving a drain will be separately analyzed in addition to those being included in the intention-to-treat analysis of that group and the group also being analyzed in a per-protocol analysis. Missing data will not be imputed.

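### Leaving every withdrawn patient out of the analysis is incompatible with the unqualified intention-to-treat statement and, in an open-label trial, lets exclusion depend on arm and outcome

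*Protocol article*

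**What the plan says.** Four places in the protocol article bear on this point.

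- Section {26b}, on consent for data use, gives the reason: "The consent form does not ask participants whether they agree to the use of their data if they choose to withdraw from the trial". It then draws the rule: "Consequently, data from patients who withdraw will not be included in the analysis". The rule has no time limit, so it covers outcomes recorded before withdrawal, and it is not confined to the primary endpoint.
- Section {20a}, on statistical methods: "The statistical analysis will follow the intention-to-treat principle". No exception for withdrawals is stated.
- Section {20c}, on non-adherence and missing data, keeps no-drain patients who received a drain in the intention-to-treat analysis of their allocated group. It then states: "Missing data will not be imputed".
- Section {17a}, on blinding: "The DRAIN1 trial is an open-label trial".

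On the likely amount of loss, section {18b} says "Due to the short follow-up period (90 days), complete follow-up is anticipated without the need for specific retention measures", and adds of this single-event intervention that "the dropout rate is expected to be low". The sample size section {14} allows 10% for dropout and loss to follow-up combined.

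**The concern.** An analysis that drops allocated patients because of something that happened after allocation is not an intention-to-treat analysis. Section {20c} shows that the term is meant in its usual sense, since crossovers stay in their allocated arm. Withdrawals are handled in the opposite way, and with no imputation nothing in the stated plan brings them back.

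The choice of population matters because of when withdrawal can happen. The intervention ends with the operation, so a withdrawal after allocation falls in the period when complications are observed, and in an open-label trial patients can know their arm. If patients with a complication in one arm are more likely to withdraw, the events removed are ones the trial has already seen, and the comparison shifts in favour of that arm. The 10% allowance in the sample size restores precision; it does not correct bias.

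This is not a detail left to an unseen analysis plan. The article fixes the rule and grounds it in the consent form, and an analysis plan cannot restore data that the trial considers it has no consent to use.

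**Working it through.** **The plan's own figure.** The documents give no withdrawal rate. The nearest figure is the 10% allowance. Taking the stated 133 per group as given, 2 × 133 = 266 and 266 / 0.90 = 295.6, that is 296, consistent with the planned 300. A 10% loss would leave 270 of 300. This combines dropout and loss to follow-up, so it serves below only as the upper end of an assumed range.

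**Inputs.**
- From section {14}: 300 patients, taken as 150 per arm; 50% morbidity with a drain; a target of 35%, hence a 15-point difference; two-sided 5% level.
- Assumed: no true effect (p = 50% in both arms); withdrawals only in the no-drain arm; share withdrawn w = 2%, 5% or 10%; morbidity among withdrawers q = 50%, 75% or 100%.

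**Formulas.** After exclusion, the expected observed rate in the affected arm is

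o = (p − w·q) / (1 − w),

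and the spurious difference is d = p − o. For the two-sided test with n₁ = 150 and n₂ = 150(1 − w), let se₀ be the pooled standard error and se₁ the unpooled one. Then

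type I error = 1 − Φ[(1.96·se₀ − d)/se₁] + Φ[(−1.96·se₀ − d)/se₁].

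**One case in full** (w = 10%, q = 100%):
- o = (0.50 − 0.10)/0.90 = 0.4444, so d = 0.0556, with n₂ = 135.
- Pooled rate = (75 + 60)/285 = 0.4737.
- se₀ = √[0.4737 × 0.5263 × (1/150 + 1/135)] = 0.0592.
- se₁ = √[0.25/150 + 0.4444 × 0.5556/135] = 0.0591.
- Upper tail 0.153 plus lower tail 0.002 gives 0.155.

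**Results.**

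| Withdrawn, no-drain arm | Morbidity among withdrawers | Observed no-drain rate | Spurious difference (points) | Two-sided type I error |
|---|---|---|---|---|
| 2%, 5% or 10% | 50% | 50.0% | 0.0 | 5.0% |
| 2% | 75% | 49.5% | 0.5 | 5.1% |
| 5% | 75% | 48.7% | 1.3 | 5.6% |
| 10% | 75% | 47.2% | 2.8 | 7.5% |
| 2% | 100% | 49.0% | 1.0 | 5.35% |
| 5% | 100% | 47.4% | 2.6 | 7.3% |
| 10% | 100% | 44.4% | 5.6 | 15.5% |

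If the withdrawals were all in the drain arm, the same sizes would apply with the sign reversed.

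**When there is no bias.** If withdrawers have the same morbidity as their arm (q = p), then o = p. If w and q are equal in both arms, the observed difference is (p₁ − p₂)/(1 − w), which is zero when there is no true effect. For example, 15 withdrawals per arm at 80% morbidity give (75 − 12)/135 = 46.7% in each arm.

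**The case against.** The strongest objection is that the exclusion follows from the consent given. By March 2025, 220 of 300 patients had been included under protocol version 1.0 (Trial status), and for them the rule cannot be edited away. Loss should also be small: there is one intraoperative intervention, follow-up is 90 days, dropout is expected to be low, and allocation waits until the decision to resect, which section {16b} says is meant to reduce dropouts. The precise analysis set and the sensitivity analyses are commonly left to an analysis plan. All of this stands as a limit on the size of the problem and on the remedy. It does not reconcile a stated exclusion with an unqualified intention-to-treat claim.

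Four stronger readings are tempting, and the documents do not support them.

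- A reader might infer that arm-related loss has occurred, or that the data are erased. The text says only that they are not analysed, and no withdrawals are reported.
- A reader might take 10% as the withdrawal rate. It is a combined planning allowance.
- A reader might see a second contradiction in section {18b}, which says of data after withdrawal that "no specific plan exists for handling such data". Having no plan to use such data and not analysing them can be read together.
- A reader might construct a larger bias from 15 withdrawals per arm with opposite selection, 20% morbidity among drain withdrawers and 80% among no-drain withdrawers: (75 − 3)/135 = 53.3% against (75 − 12)/135 = 46.7%, or 6.7 points. If complications prompt withdrawal, morbidity among withdrawers should be above average in both arms, so this case does not fit the mechanism.

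**Conclusion.** The concern holds as a contradiction between the withdrawal rule in section {26b} and the analysis principle in section {20a}, with no remedy in section {20c}. As written, the primary analysis covers randomised patients who did not withdraw, while carrying the intention-to-treat label.

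The numerical consequence is conditional. Against a 15-point target, the spurious difference is about 0.5 to 5.6 points and the type I error about 5.1% to 15.5%. This rests on no true effect, 150 per arm, all withdrawals in one arm, 2% to 10% withdrawn in that arm, and 75% to 100% morbidity among them. Neither the withdrawal share nor the morbidity among withdrawers comes from the documents. At 2% withdrawal the effect is 0.5 to 1.0 points, and it vanishes if withdrawal is unrelated to outcome. If the expectation of low dropout is met, the bias is probably small, but the article states no step that would show this.

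**What to change.** 1. **Reconcile sections {26b} and {20a}.** Define the intention-to-treat set as all patients whose allocation was opened, analysed in the allocated arm. If withdrawn patients' data cannot be used under the existing consent, describe the primary analysis as being on a modified set.
2. **Make the loss visible and bound it.** Report withdrawals by arm and timing. Add a best-case/worst-case or tipping-point sensitivity analysis of the primary endpoint that keeps withdrawn patients in the denominator of their arm.
3. **Change the consent text prospectively.** For patients still to be enrolled, provide that data collected up to withdrawal are kept. Limit the exclusion sentence in {26b} to patients who consented under the earlier form; deleting it would leave those patients without a rule or imply use of data their consent did not cover.

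**Cost.** One extra analysis, an ethics amendment with redistribution to sites by the route in section {25}, and two consent regimes within one trial. At the March 2025 count, 300 − 220 = 80 patients remained to be enrolled. Recruitment has been continuing, so fewer may now be reachable by step 3. Steps 1 and 2 do not depend on that number.

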## Interventions

### Explanation for the choice of comparators {6b}

The primary endpoint, surgery-related morbidity, was chosen as the main comparator because morbidity in pancreatic surgery presents a significant burden for patients and may potentially hinder additional systemic treatment when indicated.

### Intervention description {11a}

All patients will undergo pancreatoduodenectomy (PD) according to the local standards of each participating site. In the treatment group (no drain), patients will not receive a drain intraoperatively, while the control group (traditional treatment) will receive a drain at the end of the surgical procedure. The type of drain and its postoperative management will be determined by each center’s standard practices. Adherence to the study protocol will be ensured by treating all included patients as intended in both the treatment and control groups, and by providing appropriate follow-up as outlined in the study protocol.

### Criteria for discontinuing or modifying allocated interventions {11b}

If the operating surgeon deems a drain necessary during the procedure, the patient will be removed from the allocated group and analyzed separately, in addition to intention-to-treat and per-protocol analyses. The decision to place a drain despite the patient meeting preoperative inclusion criteria and being randomized to the no-drain group is based solely on the surgeon’s clinical judgment rather than predefined criteria.

### Strategies to improve adherence to interventions {11c}

As the intervention is an intraoperative drain placement or not, no continuous measures are available or needed in order to adhere to interventions for individual patients.

### Relevant concomitant care permitted or prohibited during the trial {11d}

Participation in DRAIN1 does not influence other parts of the medical and surgical care of the participants.

### Provisions for post-trial care {30}

No provision is provided for trial participation; the participants are incurred by Swedish health care insurance.

### Outcomes {12}

#### Primary endpoint

The primary endpoint of the study is the overall morbidity rate, classified according to the Clavien–Dindo classification. The study hypothesis is that omitting intraoperatively placed intra-abdominal drains reduces the morbidity rate. Given the significant morbidity associated with pancreatic surgery, which may hinder the administration of adjuvant chemotherapy when indicated, this endpoint is clinically well-justified.

#### Secondary endpoints

Mortality rate: defined as in-hospital mortality, 30-day mortality, and 90-day mortality.Severe morbidity rate: classified as Clavien–Dindo grade > 3a.POPF rate: defined according to the ISGPS criteria [29].Intra-abdominal abscess rate: defined as a fluid collection with infectious signs on radiological imaging.Wound infection rate: defined by clinical signs such as redness or purulent discharge.Delayed gastric emptying rate: classified according to the ISGPF definition [30].Post-pancreatectomy bleeding rate: defined according to the ISGPF criteria [31].Rate of interventional radiology procedures: defined as interventions requiring radiologic guidance, such as ultrasound-guided drain placement or angiographic procedures.Need for reoperation.Length of hospital stay (in days).Readmission rate within 90 days.

The study results will be submitted for publication upon completion, regardless of the magnitude of the findings.

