However, certain limitations must be considered. First, the lack of standardization in surgical indications, procedures, and postoperative treatments introduces heterogeneity. While this may improve external validity, it also increases susceptibility to bias. Second, the COVID-19 pandemic reduced the enrollment rate, which may affect results due to evolving treatment approaches for pancreatic head tumors. The superiority design of the trial could be questioned given the perceived benefits with no drain for a patient. However, when this trial was designed there was a strong drain policy in most pancreatic centers and a non-inferiority design was deemed too weak for clinically meaningful results. The final allocation of study participants in the operating room may induce a selection bias as events during surgery might prevent surgeons from enrolling certain patients. This was included in the study plan as a safety measure and reasons for not allocating patients as well as their outcomes were documented.

Another limitation is the absence of standardized early drain removal in the control group. However, this is unlikely to impact the study results significantly, as participating centers have adhered to early drain removal protocols for over a decade when no POPF signs are present. Additionally, since the trial was designed nearly a decade ago, newer predictive models for POPF have emerged. The selected model may be subject to criticism, as some may argue that other models are more relevant.

Lastly, at the time of trial initiation, minimally invasive PD was not performed in Sweden and was therefore not included in the protocol.

Despite these limitations, the study is expected to provide valuable insights into the necessity of routine drain placement in patients with low to intermediate risk for POPF. The findings may contribute to a shift in clinical practice, leading to more patients being treated without routine intraoperative drain placement.

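### The drain is also a means of seeing a leak and, by design, only controls have one, so low-grade fistula can be recorded more readily in the drain arm; the POPF comparison is most exposed

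*Protocol article*

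**What the plan says.** Under Intervention description {11a}, in the no-drain group "patients will not receive a drain intraoperatively, while the control group (traditional treatment) will receive a drain" at the end of the operation. The same section adds: "The type of drain and its postoperative management will be determined by each center’s standard practices". Sections {11b} and {20c} allow the surgeon to place a drain in a patient randomized to no drain; that patient stays in the no-drain group for the intention-to-treat analysis.

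On outcomes, the Primary endpoint section says: "The primary endpoint of the study is the overall morbidity rate, classified according to the Clavien–Dindo classification". No minimum grade is given; severe morbidity (above grade 3a) is a separate secondary endpoint. The hypothesis is that "omitting intraoperatively placed intra-abdominal drains reduces the morbidity rate". Postoperative pancreatic fistula (POPF) is a secondary endpoint: "POPF rate: defined according to the ISGPS criteria". No grade or common detection rule is stated.

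On assessment, section {17a} says "The DRAIN1 trial is an open-label trial", and section {18a} has local surgeons and research nurses collect the data. Section {18a} also announces a description of outcome assessment further on, but none follows in the article.

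Two further statements matter. The Discussion says that "participating centers have adhered to early drain removal protocols for over a decade when no POPF signs are present". Section {6b} describes the endpoint differently from the Outcomes section: "The primary endpoint, surgery-related morbidity, was chosen as the main comparator".

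**The concern.** The randomized item is both the treatment under test and a window onto the outcome. A drain shows what comes out of the abdomen; a patient without one offers no such view unless something prompts imaging, a puncture or a reoperation. A leak with little or no clinical consequence can therefore be noticed in one arm and missed in the other.

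The endpoint definitions give no protection. POPF is compared without a grade limit, and overall morbidity has no lower threshold, so the low-grade events for which detection is likely to differ most are not excluded. Outcome collectors know the allocation. Extra recording in the drain arm would look like a benefit of leaving the drain out, which is what this superiority trial sets out to show. The limitations in the Discussion cover early drain removal, selection in the operating room and the choice of risk model, but not unequal detection.

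**Working it through.** **1. The text, step by step.**
- Who can be observed through a drain: controls by design, plus no-drain patients given a drain by the surgeon ({11a}, {11b}, {20c}). Access is unequal but not exclusive.
- Is drain handling tied to looking for fistula? Yes. The Discussion makes early removal conditional on there being no POPF signs.
- Is POPF limited to events with consequences? Not stated.
- Does a drain-only finding count towards overall morbidity? Neither stated nor excluded.
- Is assessment arm-neutral or blinded? No such rule is stated.
- What is collected in both arms without needing a surgical drain? Abscess on imaging, radiologic intervention, reoperation, readmission, severe morbidity and death (Secondary endpoints).

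**2. The plan's own figure.** The article gives no rate of POPF or of drain-only findings, so there is nothing of that kind to reproduce. The only plan figure used is 133 per group (Sample size {14}), taken as stated. For 50% vs 35% with 80% power and a two-tailed 5% level, the usual pooled formula gives 170 per group; 133 fits a one-sided 5% calculation (134). That mismatch is a separate matter and neither supports nor weakens this point.

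**3. Illustration under assumptions.** Assume no true effect, with true morbidity p0 = 45% in both arms. Let x be the share of otherwise event-free drain patients counted only because of a drain finding. Both 45% and x are assumptions.

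- Recorded drain-arm rate: p1 = 0.45 + 0.55x; difference d = 0.55x; p̄ = (p1 + p0)/2
- SE0 = √[2p̄(1 − p̄)/n]; SE1 = √{[p1(1 − p1) + p0(1 − p0)]/n}; n = 133
- Chance of a significant result favouring no drain (two-sided 5% test) = Φ[(d − 1.96·SE0)/SE1]

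For x = 10%: p1 = 0.505, d = 0.055, p̄ = 0.4775, SE0 = 0.06125, SE1 = 0.06116. Then (0.055 − 0.12005)/0.06116 = −1.064, and Φ(−1.064) = 0.144.

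| x | Recorded, drain | Recorded, no drain | Difference (points) | False significant benefit |
|---|---|---|---|---|
| 0 | 45.0% | 45% | 0 | 2.5% |
| 5% | 47.75% | 45% | 2.75 | 6.5% |
| 10% | 50.5% | 45% | 5.5 | 14.4% |
| 15% | 53.25% | 45% | 8.25 | 26.9% |
| 20% | 56.0% | 45% | 11.0 | 43.4% |

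**4. Sensitivity to the assumptions.** At x = 10% the result is 19.2% with true morbidity of 35% and 12.6% with 50%. With 150 per arm and 45% it is 15.7%. Stated as an excess in percentage points, 5 points gives about 13% and 10 points about 37–38% (133 per arm, true morbidity 35–50%). Those excesses are one third and two thirds of the 15-point effect the trial is sized for.

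**The case against.** The strongest reply is that the mechanism rests on what the cited fistula definition contains, and the article does not reproduce it. A reader might infer that the diagnosis is made from drain fluid or from how long drainage lasts, so that the event cannot occur without a drain. The documents do not support this: they give neither the criteria nor the edition or grades meant, and patients in the no-drain arm may receive a drain. The point does not need that inference. It needs only unequal access to drain observation and endpoints without a grade limit, and both are in the text.

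A second tempting inference is that the primary endpoint is biased. No section says that a drain finding without clinical consequence is graded as a complication. This objection stands, and it is why the size for the primary endpoint is unknown.

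Third, the direction is not settled. In an open-label trial, no-drain patients may be imaged more, which would push the other way. Entry is limited to a risk score of 10 or less, and early removal is reported as usual when no POPF signs are present; both limit drain-only findings. Morbidity truly caused by a drain is the effect under study, not a detection artefact. All of this stands and limits the size.

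Fourth, event-coding rules may sit in the full protocol or analysis plan, which are not shown. If they do and are arm-neutral, the point shrinks to citing them. The article nevertheless fixes the endpoints without a limit and announces an assessment description that it does not contain.

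Finally, *surgery-related* appears only in a rationale sentence, and no attribution procedure is described. That is a wording conflict to reconcile, not evidence that events are being attributed unblinded.

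**Conclusion.** The point holds as an uncontrolled risk of unequal detection, not as a demonstrated bias. As written, the plan allows low-grade leaks or drain-only findings to be recorded more readily in the drain arm, in the direction of the hypothesis. The any-grade POPF comparison is the most likely to be affected. For overall morbidity the effect could be anywhere from nil to material, because the documents do not say whether such findings count and give no rate for them.

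The 6.5%, 14% and 43% figures show sensitivity only. They depend on an assumed 45% true morbidity, assumed drain-only shares of 5%, 10% and 20%, no true effect and no offset from extra imaging. They are not estimates for this trial. The change is worth making because it is cheap and because a positive result would otherwise be open to this alternative explanation.

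**What to change.** - **POPF.** Make the between-arm comparison one of clinically relevant POPF, judged by consequences that can be observed in both arms: a collection on imaging, radiologic intervention, reoperation or treatment given. Report any-grade POPF descriptively by arm, without a test.
- **Primary endpoint.** Keep it as overall, all-cause morbidity, and reconcile section {6b} (*surgery-related*) with the Outcomes and Sample size sections (*overall*). Redefining it more deeply after 220 of 300 inclusions in an open-label trial would raise questions of its own.
- **Sensitivity analyses of the primary endpoint, prespecified.** (a) Exclude events recorded solely from a drain finding. (b) Count only Clavien–Dindo grade II or higher.
- **Timing.** Fix and date the coding rules before any comparison by arm. Where feasible, have the coding done by someone unaware of the allocation.
- **Reporting.** Add unequal detection to the stated limitations, including that imaging may differ between arms, since relying on imaging does not by itself make detection equal.

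Cost: some re-coding from existing case records, and fewer events with less precision in the restricted analyses. The primary analysis and sample size are unaffected by these changes.
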